### Data collection

This study will run for a limited time, dashboard usage data will be collected for each practice for a month from the time of enrolment. All practices registering with the CARA network will be included in the randomisation. Dashboard usage data will be collected through Google analytics, which is an integrated part of CARA. Google Analytics provides anonymous data on the behavioural engagement with a page irrespective of who is engaging. Therefore, three identical websites (dashboards) will be set up, two of which will contain an additional landing page with a key message. At no stage IP addresses will be recorded or tracked. Table 1 shows the behavioural engagement data that will be collected.

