### Participants

General practices that register with the CARA network for access to the dashboards will be randomised (practice level) using a computer-generated system, which will allocate to either group A, B or C using 1:1:1 randomisation (Fig. 1). Practices are NOT allocated to different dashboards but to different initial landing pages from where they can access the full dashboard.

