### Outcomes

The primary outcome is behavioural engagement (measured as the number of ‘clicks’, ‘viewings’ and ‘sessions’) with the CARA dashboard after one month of dashboard usage collected through Google Analytics (Table 1).

**Table 1 Tab1:** Terminology definition of behavioural engagement outcomes (from Google Analytics [28])

Outcomes	Definition
Conversion event	Every ‘click’ on the antibiotic dashboard page (clicks include filters, comparisons with other practices and audit)
Session Conversion rate	The number of conversion events (at least one) divided by the total number of sessions*
Engaged sessions	The number of sessions* that lasted at least 10 s, had 1 or more conversion events or 2 or more page or screen views
Engagement rate	The number of engaged sessions divided by the total number of sessions*
Bounce rate	The number of sessions that were not engaged divided by the total number of sessions*
Average session duration	The average duration (in seconds) of users’ sessions*.

* A session initiates when a user opens the CARA dashboard. By default, a session ends or times out after 30 min of user inactivity

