### Data analysis

The quantitative information collected will be summarised (descriptive characteristic table) using the mean and standard deviation or, if not normal, with medians and interquartile ranges. Categorical variables will be summarised with counts and proportions. Depending on the data distribution, the continuous measures analysis will use linear regressions or generalised estimating equations for binary and count data. The *N* − 1 two-proportion test (A/B testing) will be used (for small sample sizes) to compare differences in proportions [33]. All statistical tests will be 2-tailed and significance will be set at a p-value of 0,05. Analysis will be performed using R-4.0.3® software.

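### Data collection promises usage for each practice over its own month, but the capture described identifies only the arm, so as written it supports no valid practice-level test

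*Protocol article*

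**What the plan says.** The unit of allocation is the practice. Under Participants, practices "will be randomised (practice level) using a computer-generated system", in a 1:1:1 ratio. Under Outcomes, the primary outcome is engagement "with the CARA dashboard after one month of dashboard usage collected through Google Analytics", measured by clicks, viewings and sessions. The metrics in Table 1 are counts, rates or durations of clicks and sessions; none is defined per practice.

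The Data collection section first gives every practice its own follow-up period: "dashboard usage data will be collected for each practice for a month from the time of enrolment". It then describes the data source: "Google Analytics provides anonymous data on the behavioural engagement with a page irrespective of who is engaging". The next sentence draws the consequence: "Therefore, three identical websites (dashboards) will be set up, two of which will contain an additional landing page with a key message". It adds: "At no stage IP addresses will be recorded or tracked". No practice code, login linkage or practice-specific link is described.

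Under Sample size, 29 users or practices per group (87 in total) are planned from a mean of 23.6 clicks and an SD of 14.8. Under Data analysis, "the continuous measures analysis will use linear regressions or generalised estimating equations for binary and count data", with an N − 1 two-proportion test for proportions and two-sided testing at 0.05.

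**The concern.** A usage record that carries only the website it came from can be assigned to an arm but not to a practice. Three things that the plan relies on then have no source.

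- **The follow-up window.** Practices enrol at different times. The second month of an early practice and the first month of a later one arrive in the same site traffic, and nothing in the record separates them.
- **Non-use.** A practice that never opens the dashboard generates no record, although non-use is a result of interest in a study of engagement.
- **The variance.** The between-practice SD, or median and interquartile range, needs a value for each practice. Generalised estimating equations that respect the randomisation need to know which records share a practice.

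The stake is the primary comparison. If tests are run on clicks or sessions because nothing else is available, their standard errors ignore the correlation of records within a practice, and a landing page may be declared better when the difference is only variation between practices.

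**Working it through.** **The plan's own figure.** 3 × 29 = 87 agrees with the stated total. The 29 itself does not follow from the stated inputs: 10% of 23.6 is 2.36 clicks, and with SD 14.8, two-sided 5% and 80% power (the article states no power) a two-group comparison needs 618 per group. That is a separate matter. Here 29 is used only as the planned group size.

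**Reading the text.** If the practice were attached to each usage record, the arm would follow from the randomisation list, and no further device would be needed to tell the groups apart. The article instead presents the three websites as the consequence of the anonymity. They therefore stand in for a practice identifier, and they supply the arm only.

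**Illustration for clicks.** Inputs: mean m = 23.6 and SD s = 14.8 (Sample size section); n = 29 per group; two-sided 5%. Assumption: m and s describe clicks per practice over its month. They come from a usability test, so this is illustrative.

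1. Variance-to-mean ratio: s²/m = 219.04 / 23.6 = 9.28. Independent (Poisson) clicks would give 1.
2. Standard error of a difference in mean clicks from practice-level data: s√(2/n) = 14.8 × √(2/29) = 3.89.
3. Standard error if clicks are treated as independent: √(2m/n) = √(47.2/29) = 1.28. Each site would hold about 29 × 23.6 = 684 clicks.
4. Ratio: √9.28 = 3.05. The second standard error is about three times too small, and n cancels from this ratio.
5. Actual type I error of the nominal 5% test: 2[1 − Φ(1.96/3.05)] = 2[1 − Φ(0.64)] ≈ 52%.

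**Range.** Keep m = 23.6 and let the between-practice coefficient of variation (CV) vary (assumption), so that the variance-to-mean ratio is CV² × m:

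| CV | Ratio | Type I error |
|---|---|---|
| 0.30 | 2.12 | about 18% |
| 0.63 (14.8/23.6) | 9.28 | about 52% |
| 1.00 | 23.6 | about 69% |

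**Session proportions under the two-proportion test.** The design effect is 1 + (k − 1) × ICC, for k sessions per practice and intra-practice correlation ICC. The article gives neither. Assuming k from 3 to 10 and ICC from 0.05 to 0.30:

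- k = 3, ICC = 0.05: design effect 1.10, type I error about 6%.
- k = 10, ICC = 0.30: design effect 3.70, type I error about 31%.

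**The case against.** The strongest reply is that the article does state that data will be collected for each practice, and that a condensed article may leave tagging details to the full protocol. The phrase about who is engaging could mean the individual staff member, which is compatible with practice-level capture. The platform must also know which practice it serves, since practices view their own data there (Recruitment section). This reading is possible. But it leaves the three websites, introduced as the consequence of anonymity, without a purpose for attribution. If a practice tag does exist, the description of the data source is misleading and needs correcting anyway.

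A reader might infer more than the text supports:

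- **Only three site totals would remain, and no standard error could be computed.** The article does not say so. Table 1 defines session-level measures, and the Background lists returning users among the Google Analytics indicators, so session- or user-level records may exist. Standard errors could then be computed. They would not be valid for a practice-randomised comparison, because users and sessions could not be grouped into practices.
- **Arm totals would be confounded by the number of active practices and their time on the system.** The number randomised to each arm is known, so a total per randomised practice can be formed, with non-users in the denominator. Enrolment timing is balanced in expectation, and activity after allocation is part of the effect. What changes is the quantity estimated, since use beyond the first month is included, and its precision, which could not be assessed properly.
- **The excess exposure could be quantified.** The article says only that the study runs for a limited time, so no recruitment period is available for this.

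It is also fair that the Data analysis section does not name the practice as the unit of analysis. That follows from the randomisation and the per-practice window.

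**Conclusion.** The point holds as an internal contradiction in the Data collection section. A one-month window for each practice is promised, and the capture described cannot attribute usage to a practice. Followed as written, the plan gives no per-practice month, no individual record for practices without use, and no valid practice-level standard error.

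The size depends on how the data would be tested. For clicks treated as independent, type I error is about 52% if the planning mean and SD apply to practice-months, and about 18% to 69% for a between-practice CV of 0.3 to 1.0. For session proportions it is about 6% to 31% under the assumed session numbers and correlations. These figures are illustrations; the contradiction does not depend on them.

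It does not follow that a practice-level outcome is impossible. A practice tag that the article does not describe would resolve the problem, but the text would then have to say so. Because untagged usage may not be attributable afterwards, this should be settled before usage data are collected.

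**What to change.** - **Capture.** Attach a random, non-identifying practice code to every analytics event, or use a practice-specific link or the platform's own server log. No IP address is needed.
- **Derivation.** Using each practice's enrolment date, derive its clicks, views and sessions within its own month, with zero for practices that did not use the dashboard.
- **Analysis.** Analyse one record per randomised practice, and name the practice as the unit in the Sample size and Data analysis sections.
- **Text.** State in the Data collection section how usage is linked to a practice, and reconcile the anonymity wording with it.

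The cost is that usage data become pseudonymous at practice level rather than fully anonymous, so the terms and conditions must be updated as well. The tracking change itself should be modest, because the platform already shows each practice its own data. The article does not show whether further approval would be needed.

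If the sponsor prefers to keep the data anonymous, the Sample size, Data collection and Data analysis sections should be restricted to a descriptive comparison of the three sites, without significance tests.

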### Data analysis

The quantitative information collected will be summarised (descriptive characteristic table) using the mean and standard deviation or, if not normal, with medians and interquartile ranges. Categorical variables will be summarised with counts and proportions. Depending on the data distribution, the continuous measures analysis will use linear regressions or generalised estimating equations for binary and count data. The *N* − 1 two-proportion test (A/B testing) will be used (for small sample sizes) to compare differences in proportions [33]. All statistical tests will be 2-tailed and significance will be set at a p-value of 0,05. Analysis will be performed using R-4.0.3® software.

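### The N − 1 two-proportion test, applied to the per-session rates of Table 1, treats sessions as independent although practices are randomised; if sessions within a practice are correlated, its type I error exceeds 5%

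*Protocol article*

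**What the plan says.** All of this is in the Method section of the protocol article.

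- **Randomised unit** (Participants): registering practices "will be randomised (practice level) using a computer-generated system, which will allocate to either group A, B or C using 1:1:1 randomisation". The Sample size section plans 29 per group, 87 in all.
- **Proportions defined** (Outcomes, Table 1):
  - session conversion rate: "The number of conversion events (at least one) divided by the total number of sessions"
  - engagement rate: "The number of engaged sessions divided by the total number of sessions"
  - the bounce rate is its complement, with sessions again as the denominator
- **What a session is** (Table 1 footnote): "A session initiates when a user opens the CARA dashboard. By default, a session ends or times out after 30 min of user inactivity".
- **Observation window** (Data collection): "dashboard usage data will be collected for each practice for a month from the time of enrolment". The same section calls the Google Analytics data anonymous as to who is using the page, and gives this as the reason for setting up three websites, one per group.
- **Test for proportions** (Data analysis): the N − 1 "two-proportion test (A/B testing) will be used (for small sample sizes) to compare differences in proportions", two-sided at 0.05. No adjustment for practice is attached to it. The sentence before it names generalised estimating equations (GEE) for binary and count outcomes, without a cluster.

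**The concern.** A two-proportion test, with or without the N − 1 correction, assumes independent yes/no observations. A session starts whenever a user opens the dashboard, so one practice can supply several sessions in a month. Those sessions share the practice's data and working habits, and probably its users, so some correlation is plausible. Pooling them by group makes the number of sessions the sample size, although only 29 units per group were randomised.

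The standard error is then too small and the p-value too low. A few frequently used practices in one group could produce a significant difference between landing pages that is only variation between practices. The session count is itself one of the engagement measures and may respond to the landing page, so heavy-use practices would also dominate the pooled rate. The error runs towards false positives, in a comparison meant to guide dashboard design.

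**Working it through.** **Inputs from the protocol.** 29 practices per group (Sample size); two-sided α = 0.05 (Data analysis); sessions as the denominator of all three rates (Table 1).

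**Inputs assumed.** m, the sessions per practice in the month, and ICC, the correlation of the session outcome within a practice. The documents give neither, so a range is shown.

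**The plan's own figures.** For this point the plan gives only the nominal 0.05. The formula below returns 0.050 when m = 1 or ICC = 0. The 29 per group is taken as given. It does not follow from the stated inputs if 10% is relative: 0.10 × 23.6 = 2.36 clicks with SD 14.8 needs 618 per group at 80% power, two-sided. Nothing here depends on that, because the formula does not contain the number of practices.

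**Formula.** With m sessions per practice, the true variance of a group's pooled proportion is the binomial variance times the design effect

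DE = 1 + (m − 1) × ICC.

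With no true difference, the test statistic therefore has standard deviation √DE instead of 1, and

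type I error = 2 × [1 − Φ(1.96 / √DE)].

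**One case in full.** m = 8, ICC = 0.10: DE = 1 + 7 × 0.10 = 1.70; √1.70 = 1.304; 1.96 / 1.304 = 1.503; 2 × [1 − Φ(1.503)] = 0.133. Each group has 29 × 8 = 232 sessions, worth 232 / 1.70 = 136 independent ones. The N − 1 correction does not help: with N = 464 sessions it multiplies the chi-square by 463/464 = 0.998.

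**Results, equal session counts**

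| Sessions per practice (m) | ICC | DE | Type I error |
|---|---|---|---|
| 1 | any | 1.00 | 0.050 |
| 2 | 0.02 | 1.02 | 0.052 |
| 4 | 0.02 | 1.06 | 0.057 |
| 4 | 0.10 | 1.30 | 0.086 |
| 8 | 0.10 | 1.70 | 0.133 |
| 8 | 0.20 | 2.40 | 0.206 |
| 15 | 0.30 | 5.20 | 0.390 |
| 20 | 0.30 | 6.70 | 0.449 |

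**Check by simulation.** Beta-binomial data with 29 practices per group, no true difference, true proportions 0.5 and 0.7 and 20,000 replicates agreed with the formula to within about 0.013. When session counts varied between practices the error was higher: about 0.20 for a mean of 8 sessions with ICC 0.10, and up to about 0.57 for a mean of 20 with ICC 0.30.

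**Check of the remedy.** In the same simulations, a t-test on one proportion per practice (29 against 29) kept type I error between 0.044 and 0.054 in every scenario.

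**The case against.** **The unit of the test is not stated.** This is true, and the remark about small samples could suggest practices: at 4 to 15 sessions each, a group would have 116 to 435 sessions. A reader might infer from the plan that it sets sessions as the unit; it does not say so. But the protocol defines no practice-level proportion for the test to apply to. Usage data separated only by website would also yield pooled session totals. The session-level analysis is what following the text leads to.

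**GEE is already named.** This also stands, and it would be wrong to say that the plan has no method for correlated data. The cluster and working correlation could reasonably be left to an analysis plan. However, the next sentence gives proportions to the N − 1 test, so naming GEE does not remove the problem for these rates.

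**The inflation rests on assumed values.** A reader might infer that false-positive rates are certainly well above 5%, or near 40%. The documents do not support either. Repeat sessions are possible but no number is given, and at 2 to 4 sessions with ICC 0.02 the error is only 5.2–5.7%.

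**The main outcome is untouched.** A reader might infer that the primary analysis or the sample size fails for this reason. It does not. Outcomes measures engagement by numbers of clicks, viewings and sessions, and the sample size rests on clicks. The N − 1 test is for proportions. The rates do appear among the engagement outcomes in Table 1, so the point still matters for them.

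**Conclusion.** The point holds for the three session-based rates. The named test does not match the randomised unit, and using it on these rates as defined gives too many false positives whenever practices have more than one session and those sessions are positively correlated. That the session is the unit of the test is inferred from Table 1, since Data analysis does not state it.

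The size cannot be fixed from the documents. With equal session counts it runs from essentially nominal to about 45% over the assumed range, with 9–13% at 4–8 sessions and ICC 0.1. Unequal counts raise it further. It is a wrong analysis rule with a standard replacement, limited to the rates.

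**What to change.** 1. **Replace the N − 1 test for session conversion, engagement and bounce rates.** Either compute one proportion per practice and compare groups by a linear model or permutation test, or use the GEE already named, with practice as the cluster and a small-sample corrected robust variance. For the first option, state how a practice with no sessions is handled, since its rate is undefined.
2. **Keep the N − 1 test only for one-per-practice binary outcomes**, such as any click within the month (yes/no), and say that the practice is the unit.
3. **Record a pseudonymous practice code on the usage data.** Both options in item 1 need it, and the protocol describes none. Data collection speaks of data for each practice but also of anonymous data that do not show who is engaging; these statements must be reconciled. A code not captured at collection may not be recoverable.
4. **If no code can be recorded**, report the session-based rates descriptively by group, without p-values.

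The cost is a change of analysis wording, a few lines of R, wider confidence intervals and a small change to data capture, possibly including the privacy arrangements. The sample size calculation and the analysis of the counts need no change on this account.

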**Methods:**

Participating general practices can upload their practice data for analysis and visualisation in CARA dashboards. Practices will be randomised to one of three different initial landing pages: the full dashboard or one of two key messages: a between comparison (their practice prescribing with the average of all other practices) or within comparison (with practice data of the same month the previous year) with subsequent continuation to the full dashboard. Analysis will determine which of the three landing pages encourages user interaction, as measured by the number of ‘clicks’, ‘viewings’ and ‘sessions’. Dashboard usage data will be collected through Google analytics.

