## Method

### Study design

General practices will be randomised to one of three different initial landing pages (groups): the full dashboard or one of two key messages. All practices have access to the same dashboards and view identical information but two groups will be shown a key message before they can continue to the full CARA dashboard [27]. The key messages are similar and focus on one of the charts from the existing dashboard (Figs. 1 and 2):

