### Sample size

Sample size is calculated based on the conversion event (number of clicks on the interaction with the antibiotic dashboard page, see Table 1) using a comparative usability test to determine differences between group A, B and C (between-group design) [29, 30]. A comparative usability test is a method for describing and comparing the usability of more than one application [29, 30]. The variance estimation is obtained from a usability test for a similar experiment, which reported the mean number of mouse clicks for dashboard usage (mean = 23.6 and standard deviation = 14.8) [31]. A total sample size of 87 users or practices (29 per group) is estimated to be sufficient to observe a 10% difference [7, 32] with 5% statistical confidence [29, 30].

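### Three unranked primary counts are compared across three groups with every test at 0.05, so the overall false-positive chance exceeds 5% (about 12–32% if all pairs are compared)

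*Protocol article*

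**What the plan says.** - **Outcomes:** "The primary outcome is behavioural engagement (measured as the number of ‘clicks’, ‘viewings’ and ‘sessions", taken after one month of use. No order, composite or success rule is given for the three counts.
- **Study design:** "General practices will be randomised to one of three different initial landing pages (groups": the full dashboard, or one of two key messages shown before it.
- **Abstract, Methods:** "Analysis will determine which of the three landing pages encourages user interaction, as measured by the number of" clicks, viewings and sessions. All three counts therefore feed the conclusion about pages.
- **Data analysis:** "All statistical tests will be 2-tailed and significance will be set at a p-value of 0,05". Linear regression or generalised estimating equations are named for the measures, and a two-group test for proportions.
- **Sample size:** "Sample size is calculated based on the conversion event", which Table 1 defines as a click on the antibiotic dashboard page. Its purpose is "to determine differences between group A, B and C (between-group design"). It does not say whether this means an overall test, all pairs, or each message against the full dashboard.

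**The concern.** Three counts have equal primary standing, there are three groups to tell apart, and one blanket threshold applies to every test. A 5% threshold on each test does not give a 5% error rate for the question the study asks, which is whether the landing page affects engagement and which page does so. If the pages have no effect at all, several chances remain to declare a difference.

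The three counts may also disagree, for example more clicks but fewer sessions under one message, and nothing says which count decides. Outcomes and Sample size do not match on this point: the first gives three counts primary standing, while the second plans for one.

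**Working it through.** **Inputs from the article:** three primary counts (Outcomes); three groups allocated 1:1:1 (Participants); two-sided 0.05 for all tests (Data analysis); 29 practices per group (Sample size). **Not in the article:** the correlation between the counts and the contrasts to be tested. The correlation is therefore varied from 0 to 1, and each plausible set of contrasts is worked through.

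**The plan's own figure.** Its only error figure is 0.05 per test. That is also the overall rate for exactly one plan: one overall three-group test on clicks alone (simulated 5.0%).

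**Checks by hand, counts uncorrelated:**
- Nine fully independent tests would give 1 − 0.95⁹ = 37.0%. This is too high, because the three pairs within a count share groups.
- One count with three pairs, each z = (group i − group j)/√2 and sharing groups: 12.2% by simulation. Three uncorrelated counts: 1 − (1 − 0.122)³ = 1 − 0.677 = 32.3%.
- One overall test per count: 1 − 0.95³ = 14.3%.
- Each message against the full dashboard, one count: 9.1% by simulation. Three uncorrelated counts: 1 − (1 − 0.091)³ ≈ 24.9%.

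**Simulation with correlated counts.** 1,000,000 trials per correlation, three equally correlated normal measures, no true difference between pages, two-sided 0.05. Entries are the chance of at least one false significant result. The last column is the chance that some page falsely beats both others on some count.

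| Correlation | All pairs, 3 counts | Each message v full dashboard, 3 counts | One overall test per count | A page beats both others |
|---|---|---|---|---|
| 0 | 32.4% | 24.8% | 14.2% | 4.1% |
| 0.5 | 28.5% | 21.9% | 12.7% | 3.8% |
| 0.7 | 25.0% | 19.2% | 11.2% | 3.4% |
| 0.9 | 19.5% | 14.9% | 8.5% | 2.6% |
| 0.95 | 17.3% | 13.2% | 7.5% | 2.3% |
| 1.0 | 12.2% | 9.1% | 5.0% | not run |

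A check with t-tests at 29 per group (20,000 trials) gave 31.6%, 28.6%, 23.2% and 19.3% for all pairs at correlations of 0.3, 0.5, 0.8 and 0.9. The large-sample figures for the same correlations are 30.9%, 28.5%, 22.6% and 19.5%.

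**Check of the remedy.** Take clicks only: an overall test at 5%, then the pairs at 5% only if it is significant.
- If all three pages are equal, no pair can be declared different unless the overall test rejects, which happens 5% of the time.
- If only two pages are equal, just one pairwise null is true, and it is tested at 5%.
- No other case contains a true null. The family-wise error is therefore at most 5%, provided each test holds its own level.

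**The case against.** The strongest objection is that this is a condensed article about user research, with an aim worded as exploration. Contrasts, hierarchy and multiplicity handling are commonly left to a full protocol or analysis plan, and the 0.05 sentence is a standard per-test statement that does not rule out adjustment. This is fair, and the absence of an adjustment method would not be a finding by itself. What remains is what the article does state: three co-equal primary counts, a conclusion drawn from all three about which page works, 0.05 for all tests, and a sample size for one count. A hierarchy set elsewhere would have to change those statements.

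A reader might infer several stronger points that the article does not support:
- **Nine pairwise tests are planned.** This is an inference. Regression models also fit an overall group term or contrasts with the full dashboard, and the only two-group test named is for proportions, not counts.
- **A false winning page is named 20–32% of the time.** The article has no rule that one significant pair names a winner. A page falsely beating both others on some count occurs in only about 3–4% of trials for correlations of 0.9 to 0.
- **20% is a floor.** That value needs a correlation near 0.9. Counts from one practice may be more strongly related than that: at 0.95 the figure is 17%, and the limit is 12%.
- **Table 1 adds six further tests.** Its conversion event is clicks again, the table gives definitions, and nothing says every row will be tested.

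**Conclusion.** The point holds in conditional form. With three primary counts each tested at 0.05, the chance of at least one false difference is above 5% under every set of contrasts examined, for any correlation short of perfect:
- about 12–32% for all pairs over the full range of correlation;
- about 15–25% for each message against the full dashboard, correlations of 0.9 to 0;
- about 8.5–14% for one overall test per count, correlations of 0.9 to 0.

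The figures assume equally correlated, roughly normal measures analysed by practice, and no adjustment beyond the stated 0.05. They describe any false difference, not a false choice of best page. Given the exploratory aim, this is an inexpensive improvement rather than a fatal flaw.

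**What to change.** - **Outcomes:** name clicks (the Table 1 conversion event) as the single primary outcome, which is already the basis of the sample size. Make viewings, sessions and the other Table 1 metrics secondary.
- **Data analysis:** test the overall three-group difference in clicks (2 df) at two-sided 5%. Test the three pairs, each at 5%, only if that test is significant. No further correction is needed with three groups.

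The cost is rewording in two sections and the loss of primary status for viewings and sessions; no extra practices or data are needed. If the sponsor prefers to keep three primary counts with all pairs, Bonferroni over nine tests (0.05/9 = 0.0056 each) holds the overall error at 4.6% for correlation 0 and 2.8% for 0.9, but at a much stricter threshold per test.

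One condition should be confirmed first. A practice-level analysis needs clicks for each practice. Data collection says usage is gathered for each practice, but also describes the analytics data as anonymous and sets up three separate websites for that reason. The sponsor should state that practice-level counts can be recovered.
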